#### Judging criteria

The primary outcome measure will be the difference between the two plasmapheresis techniques in the variation of the TH1 (CCR6-CXCR3 +) / TH17 (CCR6 + CXCR3-) ratio over the period D0H0-D0H3 and D0H0-D7/10.

Secondary outcome measures will include the evaluation of the peripheral lymphocyte sub-populations TH2 (CCR6-CXCR3-), Treg, T4, T4 HLA-DR + , T8, T8 HLA-DR + , B, naïve (CD45RA + CCR7 +), central memory cells (CD45RA-CCR7 +), and effector (CD45RA-CCR7-) T4 and T8 cells between H0 and H3 then between H0 and D7/10 globally and according to the therapeutic plasmapheresis technique used.

If no difference is observed between the two techniques, the variations in lymphocyte phenotypes will be presented for all cycles.

The evolution of each patient’s condition will be clinically evaluated between sessions with phenotyping before and after each session. There will also be specific scores for CIPD and the tolerance of each therapeutic plasmapheresis session regarding episodes of low blood pressure, dizziness or infection. The average cost of therapeutic plasmapheresis will be defined according to each technique used.

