### Lymphocyte phenotype with flow cytometry

Lymphocyte blood cell counts (CD3 + , CD4 + , CD8 + T lymphocytes, CD19 + B lymphocytes and CD3-CD56 + NK cell) will be made in cells/μl from fresh blood samples using CYTO-STAT tetraCHROME kits with Flowcount fluorescent beads as an internal standard and tetra CXP software with a Navios cytometer (Beckman Coulter), according to the manufacturer’s instructions. Monoclonal antibodies conjugated with fluorescein isothiocyanate (FITC), phycoerythrin (PE), energy-coupled dye (ECD), PE-Cyanine5.5 (PC5.5), PE-Cyanine7 (PC7), allophycocyanin (APC), APCAlexa700, or APCAlexa750 will be purchased from Beckman Coulter and BioLegend. To measure naïve / central memory / effector CD4 + and CD8 + T-cell subsets, the antibodies will be used in the following combinations; CD197-PE/ CD45RA-ECD/ HLADR-PC7/ CD8-APC/ CD4-APCAlexa700/ CD3-APCAlexa750.

For Th1, Th2 and Th17 cells, 100 µl of total blood samples will be stained with CD4 FITC/ CXCR3-PE/ CCR6-PC5.5/ CD3-APCA750 (BioLegend). For Treg lymphocytes analysis, direct immunostaining will be performed with CD25-PE/ CD127-PC7/ FOXP3 − AF647 (clone 259D)/ CD4-APCA700/ CD3-APCA750 (BioLegend) using the PerFix-nc kit (Beckman Coulter).

Cells will be run on a Navios flow cytometer and the results analyzed with Kaluza® software (Beckman Coulter). A minimum of 20,000 lymphocytes will be gated to analyze the subpopulations. Inter-run variability will be controlled with the same batch of Rainbow 8-peak beads (Beckman Coulter).

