intensive, prospective study on a few individuals, using a pre-defined methodology,
including systematic observations, repeated measures and appropriate data
analysis is clearly indicated for this type of problem.

Single plasma exchange and DFPP may have immunomodulatory effects via various mechanisms. Plasma removal, even when replaced by frozen plasma, induces quantitative and qualitative proportions of isotypes, subclasses and glycosylation modifications in the Ig compartment that may cause immune responses at various levels [30]. Indeed, Ig effects include i) the binding of complement fragments, thereby preventing their tissue deposition [31], ii) the inhibition of lymphocyte proliferation and inflammatory cytokine production [32] iii) modulation of dendritic cell functions [33] iv) changes in inhibitory FcγRIIB expression on macrophages [34] v) an increase in the Treg/TH17 ratio [35] and vi) a modification in the diversity of lymphocytes [36].

In addition, plasma exchange also modifies the amount of soluble factors that can influence the immune system. Among these numerous factors are cytokines and chemokines. For example, the decrease in IL-12 blood concentration might reduce the Th1/Th2 ratio [37]. The same is true for DFPP concerning soluble immune mediators larger than immunoglobulins. Finally, membrane contact in the course of the filtration may also influence immune activation [18]. For all these reasons, we will monitor T-cell differentiation (naïve, memory and effector subpopulations), activation (HLA-DR expression), and CD4 + T cell subpopulations (TH1, TH2, TH17, and Treg), as well as B-cell and NK cell populations.

Finally, as far as we know, no previous studies comparing the efficacy of single plasma exchange and DFPP integrating the medico-economic aspect of these two treatments have ever been published. The results of our study should lead to a better understanding of the action mechanisms of these two techniques. Considering that these are the two main treatments available for CIDP, once we have a better grasp of them, we will be able to offer the right treatment to each patient and ultimately treat these patients in the most cost-efficient way.

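### The TH2 outcome is the CCR6-CXCR3- remainder of all CD4 T cells, with no naive/memory or positive TH2 marker, so a naive-cell shift could be reported as a TH2 effect

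*Protocol article*

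**What the plan says.** In the protocol article, under Judging criteria, the secondary outcomes begin with "evaluation of the peripheral lymphocyte sub-populations TH2 (CCR6-CXCR3"-). The definition consists of two absent receptors. The same list contains "naïve (CD45RA + CCR7 +), central memory cells (CD45RA-CCR7 +), and effector (CD45RA-CCR7-) T4 and T8 cells" as separate outcomes. All are to be examined from H0 to H3 and from H0 to D7/10, overall and by technique.

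Under Lymphocyte phenotype with flow cytometry, the helper-cell tube is described as "For Th1, Th2 and Th17 cells, 100 µl of total blood samples will be stained with" the combination "CD4 FITC/ CXCR3-PE/ CCR6-PC5.5/ CD3-APCA750 (BioLegend"). The naive/memory tube is a different one: "CD197-PE/ CD45RA-ECD/ HLADR-PC7/ CD8-APC/ CD4-APCAlexa700/ CD3-APCAlexa750". CD197 is CCR7.

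The primary outcome uses the helper tube too, but each of its subsets needs one positive receptor: "TH1 (CCR6-CXCR3 +) / TH17 (CCR6 + CXCR3-) ratio over the period D0H0-D0H3 and D0H0-D7/10".

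The Discussion offers, as an example of how plasma exchange might act, that "the decrease in IL-12 blood concentration might reduce the Th1/Th2 ratio".

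**The concern.** A subset defined only by what it lacks takes in every CD4 T cell that does not express the two receptors. The helper tube has no marker that separates naive from memory cells and none that is positive on TH2 cells. The markers the plan uses to define naive cells are in the other tube, which has neither CXCR3 nor CCR6. The two properties are never seen on the same cell.

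The TH2 and naive T4 outcomes may therefore share many cells while being listed as different biology. If one technique moves circulating naive cells and the other does not, the trial could report a TH2 difference between techniques with no TH2 change behind it. A real TH2 change could be missed because it is spread over a much larger gate. The Background itself cites earlier work in CIDP in which CD4 subsets, naive ones included, moved back towards normal after DFPP. A naive shift under one of the two techniques is thus not far-fetched, although that work had no centrifugation comparison.

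This is not a detail that an analysis plan can supply later, because a marker that was not stained cannot be recovered.

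**Working it through.** **The plan's own figure.** 6 cycles x 3 time points = 18 measures per patient, and 18 x 5 patients = 90. This agrees with the article and gives the number of helper tubes (up to 90).

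**Inputs.** The article gives the markers in each tube but no composition of the CD4 cells. The following are assumptions:
- n, the naive share of CD4 cells: 15% to 60%
- q, the share of naive cells that are CCR6-CXCR3-: 100%, with 90% as a check
- d, the share of non-naive CD4 cells that are CCR6-CXCR3-: 20% to 60%
- true TH2 cells: 10% of CD4 cells, all inside the gate

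**Step 1: naive share of the gate.** Share = nq / [nq + (1 - n)d]. With q = 100%:

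| n | d = 20% | 30% | 40% | 50% | 60% |
|---|---|---|---|---|---|
| 15% | 47% | 37% | 31% | 26% | 23% |
| 20% | 56% | 45% | 38% | 33% | 29% |
| 30% | 68% | 59% | 52% | 46% | 42% |
| 40% | 77% | 69% | 62% | 57% | 53% |
| 50% | 83% | 77% | 71% | 67% | 62% |
| 60% | 88% | 83% | 79% | 75% | 71% |

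For n = 40% and d = 30%: 40 / (40 + 60 x 0.30) = 40/58 = 69%. With q = 90% the range is 21% to 87%. Naive cells are the majority only when n exceeds d/(1 + d), which is 17%, 23%, 29%, 33% and 38% for d = 20% to 60%.

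**Step 2: a naive shift alone.** Let n rise by 5 points, with the make-up of the non-naive cells unchanged and q = 100%. At n = 40%, d = 30%:
- Gate before: 40 + 60 x 0.30 = 58.0% of CD4 cells.
- Gate after: 45 + 55 x 0.30 = 61.5%, a rise of 3.5 points.
- Non-naive double-negative cells: 18.0% to 16.5%, a fall of 1.5 points.

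In general the gate rises by 5(1 - d) points and the non-naive part falls by 5d points. For d = 20% to 50% that is a rise of 4.0 to 2.5 points against a fall of 1.0 to 2.5 points. The reported TH2 figure moves with the naive cells, and can move opposite to the cells of interest.

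**Step 3: a true TH2 change.** A 30% rise in TH2 cells adds 3 per 100 CD4 cells. At n = 40%, d = 30% the gate count rises by 3/58 = 5.2%. At n = 15%, d = 60% the gate is 15 + 51 = 66 and the rise is 3/66 = 4.5%. The smallest gate on the grid is 15 + 85 x 0.20 = 32 (3/32 = 9.4%) and the largest is 60 + 40 x 0.60 = 84 (3/84 = 3.6%). These are changes in counts. As a share of CD4 cells the signal is weaker: (58 + 3)/103 = 59.2% against 58%, a relative rise of 2.1%.

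**Step 4: the primary ratio.** If TH1 and TH17 are 30% and 20% of non-naive cells (assumed), the ratio at n = 40% is 0.60 x 0.30 / (0.60 x 0.20) = 1.5. At n = 45% it is 0.55 x 0.30 / (0.55 x 0.20) = 1.5. The factor 1 - n cancels whatever the two percentages are, provided naive cells carry neither receptor.

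**The case against.** Four points can be made on the other side.

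1. *The naive share is not known.* A reader might infer that this outcome mostly counts naive cells. The documents do not support that. They give neither the naive share of CD4 cells nor the receptor profile of naive cells, and Step 1 includes cases well below one half. Setting naive cells against true TH2 cells alone would give higher shares, but it leaves out the other double-negative memory cells, which the definition also admits. This objection stands.

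2. *Naive cells can be subtracted in aggregate.* Both tubes contain CD3 and CD4, and naive T4 is measured at the same time points. If every naive cell is double-negative, 58 - 40 = 18 recovers the non-naive part. This stands in part: a naive shift would be visible in its own outcome, so it could, not would, be taken for a TH2 effect. But the subtraction depends on q. At q = 90% the gate is 36 + 18 = 54, and 54 - 40 = 14 instead of 18. It also leaves the remainder without a positive TH2 marker.

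3. *A constant naive share causes no false difference.* Outcomes are within-patient changes, so a false effect needs a naive shift that differs by technique. That is correct. A constant share still dilutes.

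4. *Little depends on it.* TH2 is one of many secondary subsets in a five-patient proof-of-concept study. A reader might also infer that the trial plans to test the Th1/Th2 ratio. It does not: the ratio appears only as a hedged example in the Discussion and is not a listed outcome. This limits the weight of the point without removing it, since TH2 itself is listed for comparison by technique.

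**Conclusion.** The point holds for a secondary outcome. From the documents alone, the TH2 outcome is the double-negative remainder of all CD3+CD4+ cells, measured without a naive/memory marker or a positive TH2 marker. The label claims more than the panel can show.

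The size rests on assumptions. With naive cells taken to lack both receptors, their share of the gate runs from about 23% to 88%. A shift confined to naive cells moves the reported TH2 figure in the same direction at every value tried. A 30% rise in true TH2 cells at 10% of CD4 reads as roughly 5% in counts (about 4% to 9% over the grid), and as less if expressed as a share of CD4 cells. If naive cells did carry one of the receptors, the naive part of the argument would weaken, but the absence of a positive TH2 marker would remain.

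Neither a claim that the outcome is mainly naive cells nor a claim that the primary result is compromised is supported. Under the same assumption, the TH1/TH17 ratio is untouched by this route.

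**What to change.** Add CD45RA-ECD, an antibody the plan already uses in the naive/memory tube, to the helper tube, whose listed dyes leave the ECD channel unused. Report the CCR6-CXCR3- subset within CD45RA- CD4 T cells. Leave the TH1 and TH17 gates as they are defined, so that the primary outcome does not change.

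With or without that step, call the subset CCR6-CXCR3- CD4 T cells unless a positive TH2 marker is added, because removing naive cells does not make the rest TH2.

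If the panel cannot be changed, state in the label that naive cells are included, present the subset beside the naive T4 outcome, and draw no TH2 conclusion from it.

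The first option costs one more antibody in up to 90 tubes and a compensation check. The second costs wording only. Neither needs more blood, visits or patients.

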#### Sample-size calculation

For this proof-of-concept study with SCED-type methodology in conformance with the existing recommendations for this type of study [24] and, considering the rarity of the disorder under study, the inclusion of 4 to 10 patients is recommended. Therefore, 5 patients will be included.

## Discussion

This translational research study, with its original design, will help us move forwards with our understanding of the exact mechanism of how therapeutic plasmapheresis works and allow us to compare two techniques which are widely used throughout the world. Highlighting an immune-modulating effect of therapeutic plasmapheresis could provide new indications for this technique.

From a neurological viewpoint, the treatment of CIDP still represents a huge challenge involving the enrolment of only those patients with active disease and attempting to reduce or discontinue treatment to avoiding unnecessary exposure to expensive or toxic drugs. The available publications rank therapeutic plasmapheresis as the second or third line of treatment because IVIg and corticotherapy are more readily available and less invasive. However, in the light of the current health crisis provoking a huge shortage of IVIg, it has become crucial to have access to plasmapheresis, and not just as a second or third line of treatment. If there is no response to other treatments, in over 50% of cases, these patients will depend entirely on plasmapheresis. At our clinic we have adopted a side-effect profile rationale for treatment decision-making and we intend to replicate the findings from this study on a CIDP population for whom no other first line treatment is available. Moreover, proving a difference in the (hitherto undemonstrated) therapeutic efficacy of one or other of these 2 therapeutic plasmapheresis techniques, as well as tolerance and cost, would enable us improve the care of these patients.

The SCED method has been used since very early on for studies focusing on behavioral analysis, psychiatry, physiotherapy, occupational therapy or handicap [25] and has become widely developed to evaluate technological interventions [25]. This methodology resorts to individual protocols that consist of using subjects as their own controls, ensuring a quantitative approach via repeated measures. This minimizes the probability of the changes observed being the result of a non-controlled variable [24, 27, 28]. Over the last 10 years we have seen an increase
in the use of SCED methodologies to evaluate health interventions based on innovating
technologies [26] going as far as to
produce recommendations for the publication of this type of study [29]. Thus, a user-based approach
is particularly indicated for the evaluation of medical devices. Indeed an
intensive, prospective study on a few individuals, using a pre-defined methodology,
including systematic observations, repeated measures and appropriate data
analysis is clearly indicated for this type of problem.

Single plasma exchange and DFPP may have immunomodulatory effects via various mechanisms. Plasma removal, even when replaced by frozen plasma, induces quantitative and qualitative proportions of isotypes, subclasses and glycosylation modifications in the Ig compartment that may cause immune responses at various levels [30]. Indeed, Ig effects include i) the binding of complement fragments, thereby preventing their tissue deposition [31], ii) the inhibition of lymphocyte proliferation and inflammatory cytokine production [32] iii) modulation of dendritic cell functions [33] iv) changes in inhibitory FcγRIIB expression on macrophages [34] v) an increase in the Treg/TH17 ratio [35] and vi) a modification in the diversity of lymphocytes [36].

In addition, plasma exchange also modifies the amount of soluble factors that can influence the immune system. Among these numerous factors are cytokines and chemokines. For example, the decrease in IL-12 blood concentration might reduce the Th1/Th2 ratio [37]. The same is true for DFPP concerning soluble immune mediators larger than immunoglobulins. Finally, membrane contact in the course of the filtration may also influence immune activation [18]. For all these reasons, we will monitor T-cell differentiation (naïve, memory and effector subpopulations), activation (HLA-DR expression), and CD4 + T cell subpopulations (TH1, TH2, TH17, and Treg), as well as B-cell and NK cell populations.

Finally, as far as we know, no previous studies comparing the efficacy of single plasma exchange and DFPP integrating the medico-economic aspect of these two treatments have ever been published. The results of our study should lead to a better understanding of the action mechanisms of these two techniques. Considering that these are the two main treatments available for CIDP, once we have a better grasp of them, we will be able to offer the right treatment to each patient and ultimately treat these patients in the most cost-efficient way.

## Data Availability

Not applicable.

## Abbreviations

CNIL: French data protection committee
CPP: Committee for the protection of individuals
